### 3.3. Information Collection

The data will be collected through self-report forms and physical examinations carried out by the project researchers in a space provided by the educational center conditioned with temperature, humidity, and privacy. The characterization of the sample considers age, sex, course, place of residence, educational level of the parents, number of medical licenses in the last year, % of non-attendance, and use of medicines prescribed by a doctor.

The evaluations will be carried out one week before the intervention in the three groups.

### 3.4. Randomization

An intentional sample will be carried out with randomization by course of the two selected establishments.

Each educational establishment has three fifth-grade courses each, with similar socio-educational characteristics for their level. The six courses will be randomized (24 subjects per course), of which two courses will represent intervention group 1, two courses will represent intervention group 2, and two courses will represent the control group.

### 3.5. Program: “Strong Schoolchildren with Healthy Lifestyle” (EF-Salud)

#### 3.5.1. Intervention Groups

##### Group 1: Strength Training + Nutritional, Sleep, and Screen Use Recommendations (ST + NSSR)

Co-investigators of the project will directly supervise the interventions, which will be carried out on the premises of the educational centers. The management of participants in the presence of adverse events will follow the emergency protocols established by the educational center.

The strength intervention protocol will consist of mobilization exercises and strength exercises of the upper and lower extremities using elastic bands. The students will carry out specific exercises to strengthen the muscles of the shoulders, arms and forearms, hips, thighs, and legs designed by the principal researcher (a physical education teacher who is an expert in training) together with a kinesiologist who is an expert in therapeutic exercise, who will be in charge of teaching schoolchildren and teachers to correctly perform the exercises once a day for 14 min from Monday to Friday.

The nutritional recommendations will be given by a nutritionist once a week, with a duration of 10 min, which will reveal the importance, types, frequency, and portions of healthy eating for the ages and characteristics of the schoolchildren.

The lifestyle recommendations will be given by a psychologist once a week for a period of 10 min, informing the schoolchildren about the lifestyle they should follow on a daily basis, screen time, sleep time, etc. (Table 3).

**Strength exercise program**

Bilateral and unilateral strength exercises [50,51] have been selected according to frequency, intensity, and volume [43], due to their potential health benefits [52] and their efficacy regarding the increase in lean mass, the decrease in cardiovascular risk factors, ease of application, and short duration [53,54,55,56].

*Warm-up*

The warm-up consists of joint mobility exercises for the wrists, elbow joint, shoulders, hip, knee, and ankle. It will last 4 min.

*Main exercises*

The participants will perform upper extremity exercises using an elastic resistance band [57]. The choice of this rubber will be made by the expert, where the resistance does not allow them to exceed 10–12 repetitions. There will be a familiarization session with Sci-Sport elastic bands of different sizes and resistances (XS, S, M, L, XL, XXL).

During the first two months, the XS band will be used, then during the third and fourth months the S-band will be used, and finally, during the fifth and sixth months, the M band will be used [57]. The exercises will have a moderate intensity [58] rating of 4 to 5 according to the Borg CR10 scale or modified Borg dyspnea scale [59] with a total duration of 2 min.

Exercises to perform with the upper extremities:
−Elbow flexion. Main active muscle: biceps. The participants will perform 2 series of 10 repetitions with each arm.−Elbow extension. Main active muscle: triceps. The participants will perform 2 series of 10 repetitions with each arm.

*Exercise description:*

−Each child will perform the elbow flexion exercise in a sitting position. The elastic band (circular) will be located at one end on one foot which will hold it, while the other end of the band will be taken by hand. The exercise consists of flexing the elbow (which will be resting on the thigh) 10 times. Once the ten repetitions are finished, they will perform the same exercise with the other arm and repeat it in two series.−The elbow extension exercise will be performed with the same elastic band that was used in the previous exercise. This will be held at one end by the back of the chair and the other end of the band will be held by both hands. The exercise will be performed with the hands behind the head, extending the elbow above it and pointing toward the ceiling of the room. Two series of ten repetitions will be performed.

Exercises to perform with the lower extremities:

These exercises will last two minutes in total.
−Flexion–extension of hip and knee (squat). Main active muscles: quadriceps and gluteus magnus. The participants will perform 2 series of 10 repetitions of sitting down and getting up from a chair.−Knee flexion. Main active muscle: biceps femoris. The participants will perform 2 series of 10 repetitions of performing a knee flexion, standing up.

*Exercise description:*

−The children will perform squats sitting on a chair with their feet separated between 10 and 20 cm from each other. They will stand up without help to reach the bipedal position, completing 2 series of 10 repetitions, with a 30 s break between series.−The knee flexion will be performed with a circular elastic band, standing up on the side of a chair. The children will join their extremities, aligning the knees, one against the other, and proceed to flex the knee, bringing the leg back until a 90-degree angle is achieved. This exercise will be repeated 10 times with each leg, for two series.

*Stretching*

At the end of the exercises, the students will perform stretching exercises for the muscles worked in the session. A physical education teacher and a kinesiologist will give the instructions for the exercise program in the classroom.

In each session, the exercises will be reviewed according to the children’s capacity and the execution technique. The participants will receive a notebook with all the strength exercises explained in detail. In addition, the notebook will have recommendations for a healthy lifestyle and nutrition.

**Nutritional recommendations**

A nutritionist will give nutritional recommendations on Mondays at 9:00 a.m. for six months through an expository class with the support of a projector. In these workshops, the schoolchildren will be taught about carbohydrates, proteins, lipids, junk food, and sugar intake. They will receive a diptych with the types of meals recommended for children aged between 10 and 12 years in addition to unhealthy foods, such as carbonated drinks, refined sugars, etc. This information will be shared with their parents and guardians.

**Recommendations for sleeping habits and screen use:**

The recommendations will be given by a psychologist (co-investigator of the project) once a week for 10 min, informing the schoolchildren about the lifestyle they must carry out daily, the time they should use screens, and the time they should sleep.

The talks will be focused mainly on the use of screens, dream habits, and interpersonal relationships of coexistence.

The program will last six months within the educational center and will be carried out by a multidisciplinary team [13]. This intervention should improve the physical condition and lifestyle of the schoolchildren, and therefore reduce cardiovascular risk as has been shown in the literature where overweight children with high muscle strength have fewer cardiometabolic risk factors than their overweight peers with low muscular strength [32,60,61].

##### Group 2: Nutritional, Sleep, and Use of Screens Recommendations (NSSR)

The nutritional, sleep, and use of screens recommendations will be taught together with experimental group 1, so the application conditions will be the same.

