**Rh2:** 
*A combined program of muscle strength exercises, nutritional and lifestyle education related to sleep habits, and the use of screens will present better results in improving physical condition, cardiovascular risk, and lifestyles than just education on nutrition and lifestyle related to sleep habits and use of screens or to only carry out the usual school day of physical education classes of schoolchildren in educational establishments in Punta Arenas.*

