### 3.7. Statistical Analysis

All analyses will be performed using SPSS v.25 (SPSS, Inc., Chicago, IL, USA). Missing data will be handled by intention-to-treat analysis (multiple imputation method). The description will be made as measures of central tendency and dispersion (continuous variables) and as percentages (categorical variables). Using the Shapiro–Wilk test, the normality of the data will be verified, and a two-step rank transformation will be applied to the non-normal variables. Homoscedasticity will be analyzed using Levene’s test. A 2-way repeated measures analysis of variance (ANOVA) will be used to determine the effects of the interventions. The effects of the model are the group (GE1; GE2; GC), the times (pre-test; post-test), and their interaction over time (time × group). Bonferroni’s post hoc test will be applied to identify statistically significant comparisons. The effect size will be determined using Cohen’s d (<0.2 insignificant; ≥0.2 and ≤0.49 small; ≥0.5 and ≤0.79 moderate; ≥0.8 large), considering *p* < 0.05 and GraphPad Prism v8.

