* The strength exercises will be performed every day from Monday to Friday and each session will last 14 min. ** The nutritional recommendations will take place once a week and will last 10 min. *** The sleep and screen use recommendations will take place once a week and will last 10 min.

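### The 2:2:2 draw of six courses is not stated to be made within school, yet joint teaching of groups 1 and 2, and arm contrasts free of school, depend on that

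*Protocol article*

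**What the plan says.** Section 3.4 (Randomization) gives the layout and the rule: "Each educational establishment has three fifth-grade courses each", "An intentional sample will be carried out with randomization by course of the two selected establishments", and "The six courses will be randomized (24 subjects per course), of which two courses will represent intervention group 1". Group 2 and control likewise receive two courses each. No restriction by school is stated, and the draw is not described as unrestricted either.

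Section 3.5.1 says of the interventions, under Group 1: "which will be carried out on the premises of the educational centers". Under Group 2 it says that the recommendations "will be taught together with experimental group 1, so the application conditions will be the same".

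Hypothesis Rh2 is that group 1 "will present better results in improving physical condition, cardiovascular risk, and lifestyles than just education on nutrition and lifestyle", and also better results than the usual school day. It therefore rests on two contrasts: group 1 v group 2 and group 1 v control.

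Section 3.7 defines the model: "The effects of the model are the group (GE1; GE2; GC), the times (pre-test; post-test), and their interaction over time". School is not among the effects.

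**The concern.** The statement about group 2 infers equal delivery from joint teaching. Joint teaching on school premises is possible only where a school holds a course from each of the two education arms. A draw made within school guarantees that. A single draw over six courses leaves it to chance.

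The larger issue is the contrasts themselves. With two courses per arm and two schools, an unrestricted draw can put both courses of one arm in one school and both courses of another arm in the other. Arm and school are then the same thing for that contrast, and adding a school term could not separate them using those two arms. The pre-post model removes school differences that stay constant. It does not remove a difference between schools in how much children change over six months, and such a difference would enter a fully confounded contrast whole.

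The delivery setting matters less. Table 3 and its footnotes give groups 1 and 2 the same topics, frequency and duration (for example, "The nutritional recommendations will take place once a week and will last 10 min"), so separate teaching alone would probably change little.

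**Working it through.** **Inputs.** Six courses, three in each of two schools, two per arm, 24 children per course (Section 3.4); 48 children per arm (Section 2.2); model effects of group, time and their interaction (Section 3.7).

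**The plan's own figures.** 6 × 24 = 144 children and 2 × 24 = 48 per arm. Both reproduce.

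**Step 1: count the allocations, if the draw is unrestricted.**
- All 2:2:2 allocations of six courses: 6!/(2! × 2! × 2!) = 90.
- One course per arm in each school: 3! × 3! = 36 (40%).
- Every other allocation has two courses of one arm and one of a second in one school, and one of the second and two of the third in the other: 6 patterns × 3 × 3 = 54 (60%).
- Each of the 54 puts exactly one pair of arms wholly in opposite schools: 54/3 = 18 (20%) for each pair.

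**Step 2: consequences for joint teaching.**
- 36 allocations: every group 1 course has a group 2 course in its school, and the reverse.
- 36 allocations: one education course has no partner from the other education arm in its school; the other three can still be taught jointly.
- 18 allocations: groups 1 and 2 are wholly in different schools and no joint session within a school is possible.

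**Step 3: consequences for Rh2.** Group 1 v group 2 is fully confounded with school in 18 allocations and group 1 v control in another 18. The two sets do not overlap, so one of the two Rh2 contrasts is fully confounded in 36 of 90 (40%).

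**Step 4: size of the shift.** Let D be the difference between schools in mean pre-post change, in SD of change. The group 1 minus group 2 estimate shifts by:
- 0 in 36 allocations;
- +0.5D in 18 and −0.5D in 18;
- +D in 9 and −D in 9.

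The signed shifts sum to zero, so the estimator is unbiased over the draw. Any single trial is analysed with only one of these values.

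**Step 5: false-positive rate for group 1 v group 2.** D is not given in the article, so 0.1, 0.2 and 0.3 SD are assumptions. Children are treated as independent, with 48 per arm. SE = √(2/48) = 0.204 SD. Bonferroni over three pairs gives a two-sided level of 0.05/3 = 0.0167, critical z = 2.394. For a shift s, the rate is Φ(−2.394 + s/SE) + Φ(−2.394 − s/SE). The average over draws is (36 × rate at 0 + 36 × rate at 0.5D + 18 × rate at D)/90.

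| Assumed D | Shift 0 | Shift 0.5D | Shift D (fully confounded) | Average over 90 draws |
|---|---|---|---|---|
| 0.1 SD | 1.67% | 2.0% | 3.0% | 2.1% |
| 0.2 SD | 1.67% | 3.0% | 7.9% | 3.5% |
| 0.3 SD | 1.67% | 4.9% | 17.8% | 6.2% |

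**Step 6: after the fix.** One course per arm within each school leaves 36 allocations. In all of them every arm is in both schools, the shift is 0 and joint teaching is possible.

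**The case against.** The strongest reply is that the defect exists only under one reading. Three courses per school and three arms fit one course per arm per school naturally. The phrase about randomizing by course of the two establishments can mean a draw within each, and the joint-teaching statement presupposes such a layout. Figure 1 is not available here and may show it. A journal article also commonly leaves the details of a draw to the full protocol. This stands in part: a reader might infer that Sections 3.4 and 3.5.1 contradict each other, or that the draw is certainly unrestricted, and the text supports neither. What remains is that the article does state a rule, that six courses are randomized 2:2:2. Someone following it as worded could produce an allocation that defeats the joint teaching and that analysis cannot repair.

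Second, the size is uncertain. D is unknown, and Section 3.4 describes the courses as socio-educationally similar. That lowers the risk, but it concerns the children's background rather than their change over six months; the limitations in Section 5 themselves mention uneven teacher collaboration. A reader might also take 17.8% as the trial's error rate, or the shift as systematic bias. Neither follows: 17.8% needs D = 0.3 SD and a fully confounded draw, and the shift averages zero. Nor can all three arms be confined to single schools at once; this happens in 0 of 90 allocations.

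Third, a within-school draw has a price. Under an unrestricted draw, at least one group 2 course has no group 1 course in its school in 36 of 90 allocations, and the same holds for control. Under the fix, every group 2 and control course shares a school with a strength-training course. This objection stands, but its weight is small.

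**Conclusion.** The concern holds conditionally. As worded, Section 3.4 does not secure the layout on which the group 2 statement relies. If the draw is unrestricted, full joint teaching is possible in 36 of 90 allocations and impossible in 18, and one of the two Rh2 contrasts is fully confounded with school in 36, with no school term in the model. The harm is a chance imbalance, not bias over repeated draws. For D between 0.1 and 0.3 SD it raises the group 1 v group 2 false-positive rate from 1.67% to between about 2.1% and 6.2% on average, and to between 3.0% and 17.8% in the one draw in five that is fully confounded.

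These rates rest on assumed values of D and on independent children within randomized courses; the allocation counts rest only on the stated layout. If the draw was always meant to be within school, the counts do not apply and only the wording needs attention. The change should be made, because confounding of arm with school has to be prevented at randomization.

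**What to change.** State in Section 3.4: *Within each school the three courses will be randomized, one to group 1, one to group 2 and one to control.* The statement on joint teaching can then stay as it is, because each school has one course of each education arm. If this was already the intention, the sentence confirms it.

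Schools, courses, children, staff and number of sessions are unchanged. There are two small costs:
- Every group 2 and control course shares a school with a group 1 course, which slightly raises possible spillover of the strength programme. Control courses gain no new exposure to the education component: in all 90 unrestricted allocations every control course already shares its school with an education course.
- A course-level analysis that adjusts for school has 6 − 3 − 1 = 2 residual degrees of freedom rather than 6 − 3 = 3 without school (two-sided 5% critical t of 4.30 rather than 3.18). The planned child-level ANOVA is not affected in this way.

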##### Group 3: Control Group (CG)

The CG will carry out a usual school day in relation to physical education classes.

The program will last six months (Table 3) and will be carried out within the educational centers by a multidisciplinary team [13]. It is expected that this improvement can reduce cardiovascular risk, as has been shown in the literature where overweight children with high muscle strength have fewer cardio-metabolic risk factors than their overweight peers with low muscle strength [32,43,60,61].

### 3.6. Variables

#### 3.6.1. Cardiovascular Risk

*Central obesity:* It will be analyzed using a specific index highly correlated with visceral adiposity, the waist-to-height ratio (WtHr). The waist circumference will be measured, taking as reference the equidistant point between the last non-floating rib and the iliac crest [62,63].

*Nutritional status*: The nutritional status will be assessed using the Body Mass Index (BMI). These measurements will be carried out according to the standardized procedures described by the International Society for Cinematographic Anthropometry (ISAK) (58) and according to the Habicht method.

#### 3.6.2. Physical Fitness

*Lower limbs muscle strength*: It will be assessed with the long jump (cm).

*Upper limbs muscle strength*: It will be assessed with the handgrip test, using a digital dynamometer (kg).

In both evaluations, the reference values recommended by the Alpha Fitness battery for the school population will be used, in which low strength and high strength are defined according to age and sex [64,65,66].

#### 3.6.3. Lifestyle

*Screen time:* To assess screen time, the investigators will use a self-reported survey consisting of three questions: “How many hours a day do you usually watch television?”; “How many hours a day do you usually play video games on a tablet, computer, or cell phone?”; and “How many hours a day do you usually use a tablet, computer, or cell phone for purposes other than gaming, for example, email, chats, social networks, the internet, or homework?” [67].

*Sleep hygiene:* The questionnaire “Sleep Self-Report (SSR)” in its Spanish version will be used [68].

All evaluations will be carried out before and immediately after the six months of intervention. The data set used and analyzed during the study will be available from the corresponding author upon reasonable request.

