## Abstract

Background: Childhood obesity has tripled, reaching critical levels of malnutrition. This factor is directly associated with a poorer health-related quality of life of the child and adolescent population. This article presents the study protocol of the project “Strong schoolchildren with a healthy lifestyle” (EF-Salud), which seeks to analyze the effects of a multicomponent program based on muscle strength exercises, sleep nutritional recommendations, and the use of screens in Chilean educational centers with extremely cold weather. Methods: The study protocol of a randomized controlled trial with a pre- and post-test conducted according to the CONSORT statement is reported. The total sample (*n* = 144) will be schoolchildren from six different school years, four of which will perform an intervention and two control. Intervention group 1 (from two different school years) will receive a muscular strength exercise program in the classroom once a day from Monday to Friday for six months and nutritional, sleep, and use of screens recommendations once a week. Intervention group 2 (from two different school years) will receive a program of nutritional, sleep, and use of screens recommendations once per week for six months. The control group (from two different school years) will carry out their usual school day in relation to physical education classes. Before and after the intervention, the investigators will evaluate the cardiovascular risk, physical condition, and lifestyle related to sleep and use of screens. Expected results: The schoolchildren in intervention group 1 will obtain significant results in increased strength, decreased cardiovascular risk, improved sleep habits, and fewer hours of screen use compared to the other two groups.

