## 3. Procedure

Initial contact will be made with the director of education of the University of Magallanes for project approval and with the directors of the selected educational centers in order to inform them of the objectives and procedures of the intervention.

After having the authorization of the Ethics Committee of the University of Magallanes, the Department of Education, and the directors of the educational centers, training will be carried out for the research group to unify the data collection protocol and the intervention. Then, the teachers of the educational center will be trained, giving them all the information about the project, manuals, and guidelines for the activities to be carried out. They will receive the Gantt chart (Table 2).

At the end of the training, the schoolchildren will meet to give them a complete description of the project with its objectives and authorizations, and they will be invited to be part of it, for which they must sign an assent form. On the other hand, the researchers will attend a meeting with parents or legal guardians of the educational center in which they will receive all the background of the project, explaining all the steps to follow, objectives, risks, and expected achievements for the students. The researchers will invite them to give permission for the students to participate in the program by signing their consent.

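### Self-reported screen time, and probably the Sleep Self-Report, cannot separate changed behaviour from coached answers when groups 1 and 2 are compared with control

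*Protocol article*

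**What the plan says.** **Measurement.** The protocol article (3.3) names two data sources: "The data will be collected through self-report forms and physical examinations carried out by the project researchers". For screens, 3.6.3 says: "To assess screen time, the investigators will use a self-reported survey consisting of three questions"; the questions ask for usual hours per day. For sleep it says: "The questionnaire “Sleep Self-Report (SSR)” in its Spanish version will be used". No device-based or parent-reported measure is named for either. Post-tests follow directly after the six months of intervention.

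**Coaching.** Under the sleep and screen recommendations in 3.5.1, a psychologist who is also a co-investigator speaks to group 1 for 10 minutes a week, "informing the schoolchildren about the lifestyle they must carry out daily, the time they should use screens, and the time they should sleep". For group 2 the recommendations "will be taught together with experimental group 1, so the application conditions will be the same". For control: "The CG will carry out a usual school day in relation to physical education classes". Table 3 likewise shows only usual routine for control.

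**Information to families.** Section 3 (Procedure) has the children told about the project and its objectives. The parents' meeting goes further, "explaining all the steps to follow, objectives, risks, and expected achievements for the students".

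**Claim.** The Abstract expects group 1 to show "improved sleep habits, and fewer hours of screen use compared to the other two groups". Rh2, section 4 and the Discussion also expect better lifestyle results than control. The limitations in section 5 mention school timetables and uneven teacher collaboration, but not reporting bias.

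**The concern.** Two of the three arms are taught the desirable answer and the third is not. All three are then asked the question. For screen time the quantity coached and the quantity asked are the same: hours of use per day. Children in groups 1 and 2 may report fewer hours because they use screens less, because they have learned what the answer ought to be, or both. Controls have no matching reason to shift their answers.

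Randomization does not help, because the shift arises after allocation. The baseline measure does not help, because at baseline nobody has been coached. In the planned repeated-measures ANOVA (3.7), a shift present only at post-test and only in the coached arms appears as a time × group interaction, which is the pattern a real effect would give. At stake is a published lifestyle benefit over control that could arise with no change in behaviour.

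**Working it through.** **Step 1: exposure of each outcome, from the article.**

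| Outcome | Source | Coached in groups 1 and 2? | Coached in control? |
|---|---|---|---|
| Screen time | Child's own answer | Yes, hours of use | No |
| SSR | Child's own answer | Probably (talks cover sleep time and habits; items not shown) | No |
| WtHr, BMI, handgrip, long jump | Physical measurement | Not applicable | Not applicable |

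Two of six outcomes are exposed, and only where answers are compared between arms with different coaching.

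**Step 2: could a reporting shift alone reach significance?** The plan gives no figure for a reporting shift or for the SD of screen time, so there is nothing of its own to reproduce here.

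Input from the document: 48 children per arm (2.2).

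Assumptions, not in the document:
- SD of reported screen time of 2 h.
- Coached children under-report by 15, 30 or 45 minutes, with no true change.
- A Bonferroni divisor of 3, for three pairwise group contrasts. Section 3.7 names Bonferroni but not the divisor.

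Formulas:
- d = under-reporting / SD
- δ = d × √(48/2) = d × 4.899
- P(significant) = Φ(δ − z) + Φ(−δ − z), with z = 1.960 at two-sided 0.05 and z = 2.394 at 0.05/3

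| Under-reporting | d | δ | At 0.05 | At 0.05/3 |
|---|---|---|---|---|
| 0.25 h | 0.25/2 = 0.125 | 0.61 | 9% | 4% |
| 0.50 h | 0.50/2 = 0.25 | 1.22 | 23% | 12% |
| 0.75 h | 0.75/2 = 0.375 | 1.84 | 45% | 29% |

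With no reporting shift the columns would read 5% and 0.05/3 = 1.7%. The Bonferroni column is closer to the planned analysis.

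**What the calculation leaves out.** It treats children as independent, although whole courses are randomized. It compares post-test values only. In a pre-post analysis the same shift, in SDs of change, is d/√(2(1 − r)), where r is the pre-post correlation. That is larger than d if r exceeds 0.5 and smaller if r is below it. The article gives no r.

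**The case against.** The strongest reply is that this limitation belongs to almost every trial of lifestyle advice with self-reported outcomes and a usual-routine control, that blinding is not possible, and that nothing in the article is false or self-contradictory on this point. That is fair, and it is why the remedy is a narrower claim and not a new design. It does not justify counting the control contrast as a lifestyle benefit without qualification.

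Some stronger readings are tempting, but the documents do not support them:

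- **That the bias has been shown.** It has not. The SD and the under-reporting are assumed. At the planned Bonferroni level the smallest case gives 4%, below the familiar 5% though above the 1.7% per comparison.
- **That the SSR asks for the coached quantity.** Its items are not in the article, which describes it as a measure of sleep hygiene. Overlap with the talks is probable, not established.
- **That group 1 versus group 2 is free of the problem.** The talks are shared, but the strength programme in 3.5.1 gives participants a notebook that also carries lifestyle and nutrition advice, and none is stated for group 2. Group 1 also has supervised sessions five days a week. This contrast is less exposed, not shown to be unbiased.
- **That Rh1 rests on control.** Rh1 names no comparator; Rh2 does.
- **That the children are primed with expected results.** The expected achievements are mentioned for the parents' meeting. The children hear the objectives, and no difference by arm is described.
- **That the psychologist collects the post-test answers.** Section 3.1 has the psychologist trained in data collection, so it is possible, but the article does not say so.

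**Conclusion.** The point holds for contrasts with control on screen time, and probably on the SSR: reporting bias and behaviour change cannot be told apart, and the planned analysis does not separate them. Rh2 and the expected results claim more on these two outcomes than the design can support against control.

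The direction of concern is clear, since coached children have a reason to give the taught answer. The size is unknown. Under the stated assumptions, false significance ranges from about 4% to 29% at 0.05/3 and from about 9% to 45% at 0.05. That children know their arm is inferred from the nature of the interventions and the information given to them; the article makes no statement on blinding. The comparisons on WtHr, BMI, handgrip and long jump stand as planned. This is an inexpensive improvement and not a fatal fault.

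**What to change.** 1. In 3.6.3, 3.7 and section 4, with the Abstract brought into line, state that differences from control on screen time and the SSR are interpreted as differences in reported behaviour and do not by themselves confirm the lifestyle part of Rh2.
2. Describe group 1 versus group 2 on these outcomes as less exposed to reporting bias, not as unbiased. Either give group 2 the same lifestyle and nutrition notebook content or state the difference.
3. Have the post-test forms completed in the computer room already foreseen in 3.1, supervised by an already trained team member other than the psychologist who gives the talks. This reduces the pressure to give the taught answer but does not remove it.
4. Present the project's aims to children and parents in neutral terms.
5. Add reporting bias to the limitations in section 5.

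The cost is wording, a rota choice on the post-test days and, if chosen, the notebook content for group 2. No new measurement or staff are needed. The downside is a narrower claim for two of the six outcomes.
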